### Relevant concomitant care permitted or prohibited during the trial {11d}

During the trial, all concomitant treatments are accepted except CFT and CBT (including psychoeducation) for self-stigma. A participant starting psychotherapy in parallel to their participation in the protocol will be kept in the group for ethical and clinical reasons. Their data will be excluded from the study.

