### Plans to promote participant retention and complete follow-up {18b}

Patients enrolled in the study will receive a compensation (i.e., 100 euros) at the end of the last visit with the psychiatrist. To receive the compensation, participants must have completed the visits V1, V2, and V3.

For patients in the three arms, in case of premature termination of participation in the study by decision of the investigator or the patient/guardian, the self-report questionnaires including the ISMI will be administered one last time to the exiting participant, if the patient/guardian agrees. A semi-structured evaluation interview will also be conducted. For patients who quit the study prematurely, all data collected before the decision to interrupt the study will be analyzed.

A participant starting psychotherapy in parallel to their participation in the protocol will be kept in the group for ethical and clinical reasons. Their data will be excluded from the study.

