### Methods in analysis to handle protocol non-adherence and any statistical methods to handle missing data {20c}

Subjects with at least one non-missing data, for a given analysis, will be included in the analysis.

In order to minimize attrition bias, an intention-to-treat analysis and specific techniques for handling missing data will be performed.

Missing data frequency will be listed for every variable. A univariate and bivariate (i.e., for each relevant group) description will be provided. Monotone patterns will be looked for and a probable missing data mechanism (completely at random, at random, or not at random) will be identified.

Missing data will be treated according to their frequency in a given analysis. Simple deletion will be considered if the proportion of missing data is smaller than 3%. For a missing data proportion between 3 and 20%, multiple imputations will be used. For larger proportions of missing data, the relevance of each analysis will be discussed and, if required, specific models will be used.

Multiple imputations will be implemented and run directly within the Bayesian model scripts.

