Indeed, if our 12-session group program produces a significant decrease in self-stigma and shame scores and improves participants’ social inclusion in a long-term perspective, it could become an empirically assessed viable option specifically suited to the needs of people presenting with SMI or ASD, whose quality of life is diminished due to high self-stigma. Moreover, in terms of format and content, this 12-session-manualized-group CFT has many advantages. Indeed, by targeting key transdiagnostic psychological processes—i.e., self-stigma and shame—it can increase the feasibility and dissemination of the intervention to a high number of clinical contexts (e.g., community health centers, different clinical populations).

Our study protocol presents some limitations. First, the distribution of diagnostic categories might present some inevitable variability across different hospital centers involved. However, our purpose is to propose a transdiagnostic intervention. Relatedly, facilitators’ backgrounds will vary depending on the centers, with possibly different training backgrounds and clinical experiences. To account for this limit, all group facilitators will be trained by the coordinating center clinical team during a 3-day-training specific to each intervention. Second, though concomitant psychotropic medications as well as the use of adjunctive therapeutic means (e.g., self-help or counseling) will be controlled in our study, participants will not be instructed to avoid making use of them. While this might be a potential confound in the current study design, the restriction of therapeutic options would also pose an ethical concern, reduce referrals to the study and also be a threat to external validity. Therefore, by monitoring therapeutic (i.e., medication or counseling) use throughout the trial, the current study seeks to balance the internal and external validity and improve the feasibility of the study while efficiently addressing its hypotheses.

If our innovative group CFT program can effectively reduce self-stigma and shame, it may facilitate the social inclusion of a large number of people with severe mental illness and/or ASD and significantly improve their quality of life and their physical and mental health by reducing barriers to access care.

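### Excluding the data of participants who start psychotherapy during the trial contradicts the stated intention-to-treat analysis and can bias the arm comparison

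*Protocol article*

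**What the plan says.** The Protocol article sets the rule in its concomitant-care section {11d}: "A participant starting psychotherapy in parallel to their participation in the protocol will be kept in the group for ethical and clinical reasons". The next sentence reads "Their data will be excluded from the study". The section on retention and follow-up {18b} repeats both sentences.

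The section on non-adherence and missing data {20c} defines who is analysed: "Subjects with at least one non-missing data, for a given analysis, will be included in the analysis". It continues: "In order to minimize attrition bias, an intention-to-treat analysis and specific techniques for handling missing data will be performed". It makes no exception for participants who start psychotherapy.

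For people who leave the trial, {18b} does the opposite of the exclusion rule: "For patients who quit the study prematurely, all data collected before the decision to interrupt the study will be analyzed".

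Three further facts bear on the point. Participants are told their allocation ({17a}). The primary outcome, the ISMI, is a self-report questionnaire ({12}). The TAU arm receives no intervention against self-stigma (section on the passive control arm).

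**The concern.** An intention-to-treat analysis keeps each randomised participant in the allocated arm whatever happens afterwards. Taking up psychotherapy during the trial is such a later event. It may depend on the arm, since TAU participants are offered nothing for self-stigma and know it. It may also depend on how the participant is doing. If so, the people left in each arm are no longer the groups that randomisation made comparable. The imputation planned in {20c} cannot repair this if the participants have been taken out of the data altogether.

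The rule also has no time limit. The Randomization section gives TAU participants about 10 months in the study, while the primary comparison is at the end of treatment (V1). Read literally, someone who starts psychotherapy after V1 would lose a primary outcome that had already been measured.

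**Working it through.** **1. The statements side by side**

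| Participant | Handling under {11d} and {18b} | Handling under {20c} |
|---|---|---|
| Starts psychotherapy, stays in the trial | Data excluded from the study | Included in the allocated arm if any value is observed |
| Leaves the trial early | Data up to that point analysed | Included if any value is observed |

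The first row is a direct conflict. The second has none, so a participant who stays and is assessed is treated more strictly than one who leaves. The exclusion is worded for the whole study and appears twice, so it does not look like a slip. The section on additional analyses {20b} plans none, so the article offers no secondary population to which the rule might belong.

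**2. Possible size of a shift (illustration)**

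The documents give no rate of starting psychotherapy and no outcome for those who do. Both inputs below are assumptions.

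- p = fraction of one arm excluded: 0.10 to 0.15.
- δ = difference between the excluded participants' mean ISMI and the mean of their full arm: 0.2 to 0.3 points.
- Shift in the retained participants' mean, in absolute value = p·δ/(1 − p).

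Lower case: 0.10 × 0.2 / 0.90 = 0.022. Upper case: 0.15 × 0.3 / 0.85 = 0.053.

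The planned post-therapy means in the Sample size section {14} are 2.43 (TAU), 2.20 (ESS) and 2.10 (CFT). The planned differences are therefore:

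- TAU–ESS: 2.43 − 2.20 = 0.23
- TAU–CFT: 2.43 − 2.10 = 0.33
- ESS–CFT: 2.20 − 2.10 = 0.10

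| Where the exclusions fall | Contrast | Shift as share of planned difference |
|---|---|---|
| TAU only | TAU–ESS, 0.23 | 0.022/0.23 = 10% to 0.053/0.23 = 23% |
| TAU only | TAU–CFT, 0.33 | 0.022/0.33 = 7% to 0.053/0.33 = 16% |
| CFT only or ESS only | CFT–ESS, 0.10 | 0.022/0.10 = 22% to 0.053/0.10 = 53% |

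The sign depends on who is excluded. Removing participants with worse (higher) scores from an arm makes that arm look better; removing those with better scores makes it look worse.

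**3. Numbers evaluable**

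The plan's own figure reproduces: 84 × 4/3 = 112 per arm, and 3 × 112 = 336. The allowance is 112 − 84 = 28 per arm, described as covering loss to follow-up. Exclusions bring an arm below 84 only if they and the ordinary losses together exceed 28.

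**The case against.** The best defence is that a separate analysis plan may confine the exclusion to a per-protocol set. That is possible, but the article fixes the rule for the study as a whole. Any analysis plan would inherit two incompatible statements and have to override one. This is a stated conflict, not a detail left for later.

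Four stronger readings are tempting, and the documents do not support them.

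- **That the comparison will be biased, in a known direction.** More psychotherapy in TAU, or among those not improving, is plausible. But the article gives no frequency, arm pattern or reasons. It supports only that the rule can bias the comparison.
- **That up to half of the planned effect is at risk generally.** The 22–53% range applies only to exclusions falling in CFT or ESS, measured against the smallest planned contrast. For exclusions in TAU, where the motive to seek therapy is easiest to argue, the same shifts are 7–23% of the relevant differences.
- **That 10% exclusion cuts the evaluable number from 84 to about 76 per arm.** The arithmetic, 84 × 0.90 = 75.6, assumes that the whole planned loss of 28 has already occurred.
- **That the trigger is plainly wider than the restriction.** In {11d} the exclusion follows directly on a restriction limited to CFT and CBT (psychoeducation included) for self-stigma, so psychotherapy there may mean only the barred kinds. The Discussion's statement that "participants will not be instructed to avoid making use of them" concerns medication and adjunctive means such as self-help or counselling, and does not plainly contradict {11d}. However, {11a} excepts specific psychotherapies, with CBT as the example, from TAU routine care, while the Randomization section lists psychological care within TAU. What remains is real ambiguity about who would be excluded, not a proven mismatch.

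**Conclusion.** The point holds, and the text should be corrected before the analysis. The exclusion in {11d} and {18b} contradicts the intention-to-treat analysis and the inclusion rule in {20c}. Because it acts on what is most naturally read as a post-randomisation event, in an open-label trial with a self-reported primary outcome, it can bias the arm comparison.

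The conclusion rests on the contradiction alone. The illustrated shift of about 0.022–0.053 ISMI points depends entirely on the assumed 10–15% exclusion in one arm and the assumed 0.2–0.3 point difference. Actual size and direction are unknown, and no loss of evaluable numbers below 84 per arm is shown.

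**What to change.** Delete the sentence excluding these participants' data in both {11d} and {18b}. State in {20c} that all randomised participants, with all their V1 and V2 data, enter the primary analysis in their allocated arm whatever other therapy they start. Report the analysis without the affected data only as a labelled sensitivity analysis, and add it to {20b}, which at present plans none.

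Record the start date and type of any other psychotherapy. The Discussion already foresees monitoring of therapeutic use but specifies only medication and counselling, so this is a small addition to data collection.

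The sponsor must also reconcile {11a}, {11d}, the Randomization section and the Discussion on which psychotherapies are meant. That is a clinical decision and none is proposed here; the analysis only needs the definition to be the same throughout.

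The cost is a few sentences and one or two recorded items. The statistical price is some dilution of the treatment contrast by outside therapy, which the sensitivity analysis helps to show.

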### Provisions for post-trial care {30}

Strasbourg University Hospital, the sponsor of the study, has taken out an insurance policy for the entire duration of the study that covers its own public liability as well as that of any person involved in the conduct of the trial regardless of the nature of the relationship that exists between these persons and the sponsor.

### Outcomes {12}

#### Primary outcomes

The decrease in scores on the Internalized Stigma of Mental Illness Scale (ISMI) [31] will be our primary outcome. The ISMI scale has good psychometric qualities in its various language versions [20]. This measure is a 29-item self-report questionnaire with five subscales: (1) alienation, (2) endorsement of perceived stereotypes, (3) discrimination, (4) social withdrawal, and (5) resistance to stigma. The participant must select their response on a 4-point Likert scale ranging from strongly disagree (1) to strongly agree (4).

The ISMI scale will be administered before therapy (V0), at the end of therapy (V1), and 6 months after the end of therapy (V2). If CFT is efficacious in reducing self-stigma, ISMI scores will decrease significantly between V0 and V1, and this decrease will be greater for CFT than for psychoeducation (ESS) and TAU.

### Secondary outcomes

Assessment of the maintenance of self-stigma scores:• To evaluate the maintenance of effects on *self-stigma* in the three groups of treatment (CFT, psychoeducation, and TAU) at 6-month follow-up (V2) the Internalized Stigma of Mental Illness Scale (ISMI) [31] will be applied.

Assessment of the effects of treatment (CFT, psychoeducation, and TAU) at baseline (V0), post-treatment (V1), and at 6 months follow-up (V2) on target psychological dimensions and assessment of the psychological factors mediating the efficacy of CFT on the self-stigma measure:The Internalized and Externalized Shame Scale (EIS) [53] will be used to measure shame. It consists of 9 items ranging from 1 (not at all) to 4 (a lot).The Phenomenological Body Shame Scale – Revised (PBSS-R) [54] will also be used to measure body-related shame. Each of the 8 items is scored on a scale ranging from 1 (not at all) to 5 (extremely).The Self-Compassion Scale (SCS) [55] will be applied to measure self-compassion. The 26 items are scored on a scale ranging from 1 (almost never) to 5 (almost always).The Difficulties in Emotional Regulation Scale – 16 items version (DERS-16) [56] will be used to measure emotional regulation competencies. Each item is scored on a scale ranging from 1 (almost never) to 5 (almost always).The automatic avoidance tendencies toward mental disorders (VAAST) [57, 58] assesses the participants’ automatic avoidance tendencies toward mental disorders. The VAAST simulates the approach and avoidance movements of the whole self by manipulating the visual information provided to the participants. A stimulus first appears in the center of the screen in a simulated street background. Participants have to press the “move toward” or the “move away” key as a function of the stimulus category and the instructions. This complementary measure allows to circumvent some biases (such as social pressures) in the responses to the self-report scales.

Assessment of the effects of treatment (CFT, psychoeducation, and TAU) at baseline (V0), post-treatment (V1), and at 6 months follow-up (V2) on social functioning and psychiatric symptoms:• The Brief Psychiatric Rating Scale (BPRS) [59, 60] will be used to assess psychiatric symptoms. The BPRS is a rating scale which a clinician or researcher may use to measure psychiatric symptoms such as depression, anxiety, hallucinations, psychosis, and unusual behavior. The rater enters a number for each of the 24 symptom constructs that ranges from 1 (not present) to 7 (extremely severe).• The Depression, Anxiety, and Stress Short Scale – 21 items version (EDAS 21) [61, 62] will be applied to measure depression, anxiety, and stress. Each item is scored on a scale ranging from 0 (did not apply to me) to 3 (applies to me very much, or most of the time).• The Social Functioning Questionnaire (SFQ) [63] will be used to measure social functioning. It consists of 16 items divided into two subscales: (1) the frequency of occurrence for different activities/events and (2) the participants’ satisfaction regarding said activities/events. Items of subscale 1 are rated from 0 (never) to 1 (everyday), and items of subscale 2 are rated from 0 (very unsatisfied) to 4 (very satisfied).• The Barriers to Accessing Care (BACES-EN-VI) [64] will be applied to assess participants’ access to care. Only the subscale concerning barriers to accessing care related to the stigma of mental illness will be used. The 12 items of the subscale are scored using a scale ranging from 0 (not at all) to 3 (a lot).• The Recovery Assessment Scale – short version (RAS) [65, 66] will assess participants’ recovery from the disorder. It consists of 20 items ranging from 1 (strongly disagree) to 5 (strongly agree).• The Functional Remission of General Schizophrenia Scale (the mini-FROGS) [67] will assess functional remission. The clinician-researcher will rate the 4 items, using a scale ranging from 1 (does not do it) to 5 (does it perfectly).

To evaluate the *acceptability* of the active interventions (CFT and ESS):• The Credibility and Expectations Questionnaire [68, 69] will be applied to assess self-reported treatment credibility at V0. This questionnaire contains 6 items rated either from 1 to 9 or from 0 to 100% and evaluates whether the participants “think” or “feel” that their treatment will be efficient.• The Group Questionnaire [70] will be used to measure group cohesion 3 times during the intervention (sessions 1, 6, and 12). It consists of 30 items addressing the group leaders, the other group members, and the group in general. Each item is scored using a scale ranging from 1 (not true at all) to 7 (very true).• The Consumer Satisfaction Questionnaire for Psychotherapeutic Services (CSQ-8) [71] will be applied as a self-report measure assessing participants’ satisfaction at the end of the 12-week program. The 8 items are scored on a scale ranging from 1 to 4. Higher scores are indicative of elevated satisfaction.• The attendance rate will be determined by the number of group sessions attended by the patient, and the drop-out rate will be determined by the number of patients lost to follow-up in each arm. In addition to the Consumer Satisfaction Questionnaire for Psychotherapeutic Services questionnaire (CSQ 8) [71], the avoidance of participants (due to self-stigma) in several social situations during the last 6 months, and the satisfaction with the interventions will be assessed via semi-structured interviews conducted at V2 by clinician-researchers blind to the status of patients (in the Strasbourg center only, for the 3 groups—CFT, ESS, and TAU).

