**Methods:**

This seven-center trial will involve 336 participants diagnosed with a severe mental illness and/or autism spectrum disorder and reporting high levels of self-stigma. Participants will be randomized into one of three treatment arms: 12 week-treatment of compassion-focused therapy (experimental arm), 12 week-treatment of Psychoeducation (active control arm), and TAU (treatment as usual—passive control arm). The primary outcome is the decrease of self-stigma scores on a self-report scale, i.e., ISMI, at 12 weeks. Secondary endpoints include sustainability of self-stigma scores (ISMI) and self-reported scores regarding target psychological dimensions, e.g., shame and emotional regulation, social functioning, and psychiatric symptoms. Assessments are scheduled at pretreatment, post-treatment (at 12 weeks), and at 6-month follow-up. Acceptability will be evaluated via (i) the Credibility and Expectancy Questionnaire at T0, (ii) the Consumer Satisfaction Questionnaire for Psychotherapeutic Services posttreatment and at 6-month follow-up, (iii) attendance, and (iv) dropout rates.

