The purpose of our study is to evaluate the efficacy and acceptability of a transdiagnostic CFT group for self-stigma compared to ESS [30] and treatment as usual (TAU). CFT has been found to be feasible and to reduce shame in SMI including personality disorders [37], patients with psychosis [45, 46], as a transdiagnostic group [47] and, in a pilot study led by our group, in patients presenting with SMI and ASD [48]. However, CFT has not been used to specifically target self-stigma and shame in this population. Our adaptation of CFT aims to address the limitations of existing self-stigma reduction programs such as the ESS [e.g., [30]], i.e., (i) lack of superior effects when compared to active control interventions, (ii) low attendance and high dropout rates, and (iii) lack of long-term effects, which can be attributed to the fact that interventions aimed at deconstructing beliefs and did not target shame.

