#### Objectives {7}

The primary objective of our study is to evaluate the efficacy of a 12-week CFT group in decreasing self-stigma associated with severe psychiatric disorders and ASD by comparing its immediate effects to the effects of the Ending Self-Stigma (ESS) psychoeducation program [29] and to TAU.

The secondary objectives of our study are as follows:1. To evaluate the maintenance of effects on self-stigma scores in the three groups of treatment (CFT, ESS, and TAU) at 6-month follow-up (V2)2. To assess the effects of treatment (CFT, ESS, and TAU) at baseline (V0), post-treatment (V1), and at 6 months follow-up (V2) on target psychological dimensions (shame, self-compassion, emotional regulation, automatic avoidance tendencies toward mental illness)3. To assess the effects of treatment (CFT, ESS, and TAU) at baseline (V0), post-treatment (V1), and at 6 months follow-up (V2), on social functioning and psychiatric measures (psychiatric symptoms, depression, anxiety and stress, social functioning, access to care, recovery, functional remission)4. To assess the psychological factors mediating (shame, self-compassion, and emotional dysregulation) the efficacy of CFT on the self-stigma measure (V1)5. To evaluate the acceptability of the active interventions (CFT and ESS): pretreatment (V0) via a treatment credibility measure, during treatment via attrition rate, session attendance and group cohesion, and post-treatment (V1) via patient satisfaction and treatment side effects In addition, in the coordinating center, qualitative interviews will assess the acceptability of the active interventions.

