### Criteria for discontinuing or modifying allocated interventions {11b}

Participants may withdraw their consent and request to leave the study at any time for whatever reason. The investigator must document the reasons for early discontinuation as fully as possible. The investigator has the right to discontinue a subject’s participation in the study, temporarily or permanently, for any reason that is in the best interest of the subject.

Participants who prematurely discontinue the study procedure will continue follow-up in the study until the end-of-study visit scheduled in the protocol. The criteria for premature termination of participation by the investigator are long-term hospitalization (more than 1 month).

For patients in the three arms, in case of premature termination of participation in the study by decision of the investigator or the patient/guardian, the self-report questionnaires including the ISMI will be administered one last time to the exiting participant, if the patient/guardian agrees. A semi-structured evaluation interview will also be conducted.

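### The drop-out rate is defined as loss to study follow-up, so a participant who leaves the CFT or ESS group but still attends the visits is not counted

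*Protocol article*

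**What the plan says.** Under Secondary outcomes, in the list that evaluates the acceptability of CFT and ESS, one sentence defines two measures. For the first, "The attendance rate will be determined by the number of group sessions attended by the patient". For the second, "the drop-out rate will be determined by the number of patients lost to follow-up in each arm".

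Four other places bear on this:

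- Objectives {7}, fifth secondary objective, assesses acceptability of the two active interventions "during treatment via attrition rate, session attendance and group cohesion". The abstract also lists attendance and drop-out as separate acceptability measures.
- Background and rationale {6a} names "low attendance and high dropout rates" among the limitations of existing programmes such as ESS that the CFT adaptation is meant to address. The Discussion repeats the hypothesis that untreated shame explains drop-out from ESS.
- Section {11b} on discontinuation says: "Participants who prematurely discontinue the study procedure will continue follow-up in the study until the end-of-study visit scheduled in the protocol". For those whose participation ends early, it says that the self-report questionnaires "will be administered one last time to the exiting participant", if they or their guardian agree.
- Section {18b} on retention makes the 100 euro payment conditional on completed visits, not on sessions attended.

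**The concern.** Leaving a therapy group and being lost to follow-up are different events. The first says something about the therapy. The second says whether the trial could still collect data. The protocol's argument is about the first: ESS loses participants from its groups, and CFT should hold them better. The rule it fixes counts the second.

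The two would nearly coincide if everyone who left a group also left the study. The protocol is built to prevent that, since it keeps discontinuers in follow-up and pays for visits. The better the trial retains people who have stopped therapy, which is good practice for the primary analysis, the fewer of them the drop-out measure records.

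At stake is a secondary result. A CFT versus ESS comparison of drop-out would be reported as evidence on acceptability while describing visit retention.

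**Working it through.** **The protocol's own figure.** The only number tied to loss to follow-up is the allowance in Sample size {14}: 84 × 1.33 = 111.7, rounded up to 112 per group, and 3 × 112 = 336. Equivalently 84 / (1 − 0.25) = 112, so the allowance covers 25% loss. It reproduces. It concerns missing outcome data, for which loss to follow-up is the right quantity, and nothing below changes it.

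**Who is counted under the stated rule.**

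| Participant in CFT or ESS | Left therapy? | Counted as drop-out? |
|---|---|---|
| Stays in the group and attends the visits | no | no |
| Leaves the group and attends the visits, as {11b} foresees | yes | no |
| Leaves the group and is lost to follow-up | yes | yes |
| Leaves the study with a last questionnaire | yes, if before the group ends | not stated |

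The second row is the error. In addition, the rule applies to each arm and the trial has three. TAU participants have no group to leave, so a count that is equally defined for them can only be study retention.

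**Size.** Let q be the share of an arm that quits therapy and f the share of those quitters who still attend the visits. Ignoring losses among people who complete therapy:

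recorded drop-out rate = q × (1 − f)

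shortfall against therapy drop-out = q − q(1 − f) = q × f

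The protocol gives neither q nor f, so both are assumptions here. With q = 30% of 112, that is 33.6 quitters per arm:

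| f | Quitters counted | Recorded rate | Shortfall (points) |
|---|---|---|---|
| 0 | 33.6 | 30% | 0 |
| 0.25 | 25.2 | 22.5% | 7.5 |
| 0.50 | 16.8 | 15% | 15 |
| 0.75 | 8.4 | 7.5% | 22.5 |
| 1 | 0 | 0% | 30 |

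Holding f at 0.5 and varying q from 20% to 40%, the recorded rate runs from 10% to 20%, half the therapy drop-out rate throughout.

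**Effect on the comparison of CFT with ESS.** If f is the same in both arms, the ratio of recorded rates is q(ESS)(1 − f) / q(CFT)(1 − f) = q(ESS) / q(CFT). Ratio and direction are kept, and the absolute gap shrinks by the factor 1 − f. For example, with q of 40% and 25% and f = 0.60 (all assumed), the recorded rates are 0.40 × 0.40 = 16% and 0.25 × 0.40 = 10%. The gap falls from 15 to 6 points while the ratio stays at 1.6. The direction could change only if f differed between the arms, or if enough therapy completers were lost.

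**The case against.** The strongest reply is that abandonment of therapy is already recorded in the same sentence: someone who leaves after session 2 appears as 2 of 12 sessions attended. Credibility, group cohesion and satisfaction are measured as well. This stands in part. The information is not absent, and a reader who infers that the trial cannot see therapy abandonment at all goes too far. But no attendance threshold is tied to drop-out, and the protocol reports the two as distinct outcomes, so the one called drop-out remains wrong for its stated purpose.

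Second, section {11b} speaks of discontinuing the study procedure, not therapy, and it also describes participants who leave the study altogether. Some quitters will take that route and may be counted. This stands too, and it limits the error to quitters who remain in follow-up.

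Three stronger readings are tempting, and the document does not support them:

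- **That the comparison would favour the wrong therapy.** As shown above, this needs different retention of quitters in the two arms, or losses among completers. The document gives no reason to expect a particular pattern.
- **That someone who attends all 12 sessions and misses V2 is counted as a drop-out.** The definition gives no time point, and Objective 5 places attrition during treatment, so the count might stop at V1.
- **That the cited ESS trial supplies the size.** Its 43% is the share who attended at least 7 sessions, which is not a drop-out rate.

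**Conclusion.** The point holds in a limited form. As written, the drop-out rate measures study retention in each arm, although the objective and the rationale concern attrition from CFT and ESS during treatment. It misses those who quit therapy and stay in follow-up, a path that the protocol itself provides.

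The shortfall is q × f. It is zero if no quitter attends the visits and equals the whole therapy drop-out rate if all do; with an assumed q of 30% it lies between 0 and 30 points. Nothing in the document narrows that range. The calculation assumes no loss among therapy completers and counts every quitter who leaves the study as lost.

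Drop-out is one component of one secondary objective. A reader might take the point as a threat to the trial's main result, but the ISMI comparison and the sample size do not depend on it. It is still worth correcting, because the rule is stated explicitly rather than left open, and the result would be read as evidence on the weakness of ESS that CFT is meant to remedy.

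**What to change.** Replace the definition with two separately named quantities:

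1. **Therapy drop-out, CFT and ESS only:** stopping group attendance before the end of the programme, derived from session attendance. The trial team sets the cut-off and fixes it before seeing the data. Compare CFT with ESS on it using the Bayesian logistic regression already planned for binary secondary outcomes.
2. **Loss to follow-up, all three arms:** reported at V1 and at V2 as study retention, with a statement of whether participants who leave with a last questionnaire count as lost.

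This is a measurement definition. It changes no rule on who stays in or leaves a group, and no visit. The cost is one changed definition and one extra table. The protocol already counts sessions attended; if the chosen cut-off depends on which sessions were missed, the team should confirm that attendance is kept session by session and not only as a total.
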